#### Quality control

This study will be conducted according to the rules of ‘Good Pharmacoepidemiology Practice’ and the ‘Guidelines on Good Pharmacovigilance Practices’. The clinical research organisation SSS International Clinical Research GmbH (Munich, Germany) will be responsible for managing and performing all operational tasks, including setting-up, monitoring and managing the non-interventional study.

Regular data quality checks will be performed throughout the study to ensure the accuracy and completeness of recorded data, the satisfactory protection of patients’ rights and compliance with the observational plan and relevant regulatory requirements. The data management team and the medical monitor will direct any queries relating to the eCRFs to the relevant centres.

The integrity of all submitted data will be verified by signature by the responsible physician.

On-site monitoring will be performed at 20% of randomly selected sites. During the on-site visits, all patient informed consent documentation will be verified and the submitted data for 3 randomly selected patients will be quality checked against their medical records.

#### Sample size calculations

As ENCOURAGE-AF is a non-interventional study that will collect routine clinical data only, no primary parameter was defined for the sample size calculation. A sample size of 720 patients will provide sufficient precision (measured by width of 95% confidence interval [CI]) for the rates of major and CRNM Bleeding, CV death, stroke (any, ischemic, haemorrhagic) and MI during the one-year follow-up. In the randomised controlled clinical study (ENTRUST-AF PCI), an event rate of 17% was observed for the composite outcome of major or CRNM bleeding (ISTH) in patients receiving edoxaban^7^. With approximately 720 enrolled patients it will be possible to estimate the 95% CI with a precision range of ± 2.7% (resulting in relative precision of 16.1%).

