##### Bleeding events

Since bleeding event data will be collected in a different setting at baseline compared with the follow-up period, different methods for categorising bleeding events will be employed. At baseline, bleeding events will be recorded in a hospital setting and will be classified according to the International Society on Thrombosis and Haemostasis (ISTH) bleeding criteria (major, clinically relevant non-major [CRNM] or minor events^16,17^. At follow-up, patients will be questioned regarding bleeding events via telephone, therefore a different set of patient friendly categories will be used (Table 5). The patient memory aid will describe the different bleeding categories for ease of understanding. A patient’s relatives or primary care physician may be contacted to confirm death due to bleeding.

**Table 5 Tab5:** Bleeding event categories for outcome.

Evaluation	Bleeding event category
Relative or primary care doctor reported death due to bleeding	Bleeding with fatal outcome
Questions regarding hospitalisation and blood transfusions for bleeding are answered with “yes”	Bleeding requiring hospitalisation and blood transfusion
Question regarding hospitalisation for bleeding is answered with “yes”	Bleeding requiring hospitalisation
Question regarding outpatient medical intervention is answered with “yes”	Bleeding requiring medical intervention
All questions regarding bleedings are answered with “no”	Bleeding not requiring medical intervention

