Throughout the study, different methods for categorising bleeding events will be used at baseline compared with the follow-up period due to the different settings in which the data will be collected (hospital versus telephone respectively). During the follow-up, a number of factors may influence the accuracy of the reporting, which relies upon both the physicians’ interviewing techniques and the ability of patients to recall past events precisely, via telephone. The accuracy of reporting could be affected by a patient’s age and/or health status. Thus, in contrast to baseline, when bleeding events are reported in hospital, bleeding events may be under-reported during the follow-up.

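### The stated precision for n=720 refers to one-year ISTH major or CRNM bleeding, but ISTH classes are assigned only at the in-hospital baseline and follow-up bleeds are graded on a different telephone scale

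*Protocol article*

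**What the plan says.** Under Sample size calculations, the protocol article states: "A sample size of 720 patients will provide sufficient precision". Precision is judged by the width of the 95% confidence interval, and the claim is made "for the rates of major and CRNM Bleeding, CV death, stroke (any, ischemic, haemorrhagic) and MI during the one-year follow-up". Only one outcome gets a number. From the reference randomised trial, "an event rate of 17% was observed for the composite outcome of major or CRNM bleeding (ISTH) in patients receiving edoxaban", and with 720 patients this is said to give ±2.7 points, or 16.1% relative. The same section says that "no primary parameter was defined for the sample size calculation".

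Under Definitions, Bleeding events, the article describes two methods. Bleeds at baseline are recorded in hospital and classed by ISTH as major, CRNM or minor. At follow-up, "patients will be questioned regarding bleeding events via telephone, therefore a different set of patient friendly categories will be used". Those categories are in Table 5: fatal, hospitalised with transfusion, hospitalised, treated as an outpatient, and no medical intervention needed.

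The Discussion acknowledges the two methods and adds that, in contrast to the hospital baseline, "bleeding events may be under-reported during the follow-up".

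**The concern.** The precision claim names an outcome (ISTH major or CRNM bleeding) and a period (the one-year follow-up). The definitions section records that outcome only at the start of the period. From then on, bleeds are graded by what care they led to, as the patient reports it, and nothing shown says which Table 5 categories count as major or CRNM.

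Safety is a stated secondary objective, and clinical events are to be reported as frequencies with 95% intervals. If a one-year result were labelled major or CRNM, it would mix two definitions and two kinds of ascertainment. A reader who set it beside the 17% in the sample size section would be comparing different outcomes. Given the article's own warning about under-reporting, the study figure would probably look lower for reasons unrelated to the drug. The assumed rate behind the stated precision also has no support for the scale that is actually used after baseline.

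**Working it through.** **1. Reproduce the stated figure.** Inputs from Sample size calculations: n = 720, p = 0.17, two-sided 95% (z = 1.96).

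- Half-width = z × √(p(1−p)/n) = 1.96 × √(0.17 × 0.83 / 720) = 0.0274, that is ±2.7 points.
- Relative precision = 0.0274 / 0.17 = 16.1%.

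Both figures reproduce. A Wilson interval gives the same values to the precision shown. A Clopper-Pearson interval (122 events of 720) gives about ±2.8 points and 16.5%. The calculation is sound, so the question is which outcome it describes.

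**2. Set the claim against the measurement.**

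| | Precision claim | What is recorded |
|---|---|---|
| Scale at baseline | ISTH major or CRNM | ISTH major, CRNM, minor |
| Scale at 30 days and 1 year | ISTH major or CRNM | Table 5 telephone categories |
| Link between the scales | implied | none shown |

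The Schedule section says observation begins 4 to 72 hours after the guiding catheter is removed, and runs to about one year. The article does not say when the baseline bleeding window closes. If it closes by 72 hours (assumption), about 365 − 3 = 362 days carry no ISTH class.

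**3. What can and cannot be estimated as described.**

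- One-year ISTH major or CRNM rate: no.
- One severity-graded rate on a single scale from PCI to one year: no.
- Follow-up rates by Table 5 category: yes, because the 30-day and one-year contacts share that scale.
- Any bleeding from baseline to one year: yes. Both scales reach down to the mildest bleeds, reading the lowest Table 5 category as a reported bleed that needed no intervention.

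**4. Precision for a Table 5 outcome.** The article gives no rate for any Table 5 category, so the rates below are assumptions. The formula is that of step 1, with n = 720 and all patients evaluable; expected events = 720 × p.

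| Assumed rate | Expected events | Half-width (points) | Relative |
|---|---|---|---|
| 5% | 36 | ±1.6 | 32% |
| 8% | 58 | ±2.0 | 25% |
| 10% | 72 | ±2.2 | 22% |
| 12% | 86 | ±2.4 | 20% |
| 17% | 122 | ±2.7 | 16% |

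At lower rates the interval narrows in absolute terms but widens relative to the rate. The quoted 16.1% holds only near 17%.

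**The case against.** The strongest reply is that the two-scale design is deliberate, explained and disclosed. ISTH grading suits hospital data, telephone interviews need simpler categories, and the Discussion says so. Follow-up is also not purely patient recall: routine medical records are used, and relatives or the primary care doctor may be contacted. A mapping could sit in the full observational plan, the analysis plan or the supplement, none of which is shown. This tempers how firmly one can say that the rate will never be produced. It does not settle the point, because the disclosure never returns to the precision statement, and the two sections conflict as they stand.

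Several stronger readings are tempting, and here the reply is right:

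- A reader might infer that the study was sized on ISTH bleeding. The article says no primary parameter was defined, and the Study population section ties the cut from 1200 to 720 patients to slow recruitment. The 17% illustrates precision; it did not determine n.
- A reader might infer that no one-year bleeding rate can be obtained at all. Step 3 of the working shows otherwise.
- A reader might take bleeding to be the main safety result. It is one of several secondary clinical events, alongside stroke, MI, PCI, death and adverse drug reactions.
- A reader might assume a planned comparison with the 17%. The study is described as non-comparative and is meant only to complement the randomised trial.

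It is also fair to say that the stated half-width is not optimistic in absolute terms if the true rate is below 17%.

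**Conclusion.** The point holds as a contradiction between two sections. The precision figure is correctly calculated, but for an outcome that the described data collection does not record over the stated period. The missing quantity is specific: the one-year ISTH major or CRNM rate, and more generally any severity-graded bleeding rate on one scale from PCI to one year.

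The 17% cannot be carried over to the telephone categories, because both the definition and the ascertainment differ and the article itself allows for under-reporting. The size of the effect on precision depends on rates that the article does not give. Over an assumed 5% to 17%, relative precision runs from 32% to 16%, against the stated 16.1%, while the absolute half-width stays between ±1.6 and ±2.7 points.

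The conclusion rests on the article alone, and a pre-specified mapping in an unseen document would resolve most of it. Nothing here calls into question the number of patients or the primary objective on treatment patterns.

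**What to change.** 1. Restate the precision for an outcome that follow-up measures, for example fatal bleeding or bleeding that led to hospitalisation, transfusion or other medical intervention. Give it over a range of assumed rates, as in the second table of the working, instead of at 17% alone.
2. Label ISTH results as baseline, in-hospital results. Do not label one-year telephone results as major or CRNM.
3. If one severity-graded incidence from PCI to one year is wanted, choose one route and specify it before analysis. Either code baseline bleeds on the Table 5 scale as well, or define and justify a mapping between the scales. The first route needs a stated rule for patients already in hospital, since hospitalisation because of the bleed has no plain meaning during the PCI admission; prolonged stay or transfusion are possible criteria.

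The cost is wording changes and, if baseline bleeds are recoded, one derived field. No additional patients or visits are needed. The price in presentation is a less favourable relative precision wherever the assumed rate is below 17%.

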#### Statistical analysis

The patient disposition will include patients from the *All-Documented Patient Set (APS),* who have a signed and dated an informed consent form. This will summarise the number and percentage of patients in the different analysis sets including reasons for exclusion, who completed or did not complete the regular observational period (including reasons for non-completion), as well as patients who did or did not receive at least one dose of edoxaban post Index PCI. The *Baseline Analysis set* (BAS; all patients from the APS who fulfil the study eligibility criteria with any further baseline documentation) will be used to describe patient demographics and other baseline characteristics shown in Table 3 (and listed in full in Supplemental Appendix SI).

All other statistical analyses will be performed on data from the *Full Analysis Set (FAS),* consisting of all patients from the *BAS* with documentation from at least one time point post-baseline. SAS version 9.4 or higher will be used to conduct the analyses.

To address the primary objective, a descriptive analysis of data on the usage of peri- and post-procedural antithrombotic therapies, as well as other relevant concomitant medications at baseline and the two follow-up time points will be performed (to include extent of exposure and dosing regimens).

The analysis for the secondary objectives will be based on data documented for physician- and patient-reported clinical events of interest (bleeding events, stroke, MI, PCI, or death), ADRs, PROs (EQ-5D-5L questionnaire) and HRU parameters. Data for clinical events of interest will be reported as absolute and relative frequencies with 95% confidence intervals and Kaplan–Meier analyses will be performed where applicable to determine outcome risk over time. ADRs will be coded using the Medical Dictionary for Regulatory Activities coding dictionary (version 23.1 or higher) and ADR incidences will be reported. EQ-5D-5L and HRU parameters will be summarised descriptively.

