## Methods

### Study design

#### Study objectives and outcome measures

The primary objective of ENCOURAGE-AF is to gain insights into the peri- and post-procedural use of anticoagulation and antiplatelet therapy in combination with edoxaban in patients with non-valvular atrial fibrillation (NVAF) undergoing successful PCI in German routine clinical practice for up to 1 year after the procedure. The duration of exposure to and dosing regimens of the antithrombotic agents and other concomitant medications of interest used will be evaluated and any patterns of treatment use will be reported.

The secondary objective is to investigate the effectiveness and safety of edoxaban in combination with antiplatelet therapy up to 1 year after a successful PCI by reporting incidences of physician- and patient-reported clinical events of interest (bleeding events, stroke, MI, PCI, or death) and documented adverse drug reactions (ADRs). Additional secondary objectives include evaluating patients’ health-related quality of life via the five-level EQ-5D (EQ-5D-5L) questionnaire and gaining insights into patients’ health resource utilisation (HRU) with respect to hospital admissions and number of days of hospitalisation.

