#### Study population and eligibility

At study start, the study was planned to include 1200 patients enrolled from approximately 60 sites with PCI capability until end of 2021 across Germany. Due to the Coronavirus-19 pandemic, the patient recruitment was considerably slower than expected. Therefore, it was decided to prolong the recruitment for six months until end of June 2022 and decrease the sample size to 720 patients. Patients who fulfil the eligibility criteria listed in Table 2 qualify for study enrolment. For those with a staged PCI planned, eligibility will be assessed after completion of the last successful PCI.

**Table 2 Tab2:** Patient eligibility criteria.

Patient eligibility criteria
Providing written informed consent for participation in the study
Having NVAF treated with edoxaban
Undergone successful PCI
Having no planned elective cardiac intervention for the entire study duration (up to 1 year)
Capability, availability, and willingness for follow-up by telephone by the site for the entire study duration (up to 1 year)
No simultaneous participation in any other interventional study
≥ 18 years of age
Life expectancy > 1 year

*NVAF* non-valvular atrial fibrillation, *PCI* percutaneous coronary intervention.

Given that ENCOURAGE-AF is a non-interventional study, there are no specific study exclusion criteria. To allow for a meaningful differentiation between elective PCI and ACS populations, recruitment is monitored and, if necessary, adjusted in some sites to ensure that at least 25% of all enrolled patients underwent PCI for ACS.

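### The Full Analysis Set drops patients who have baseline data only from the peri-procedural therapy analysis and from the event and ADR rates, although these data are collected at baseline

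*Protocol article*

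**What the plan says.** The Statistical analysis section of the protocol article defines three nested sets.

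- The APS (patients with signed consent) serves the disposition table.
- The BAS is "all patients from the APS who fulfil the study eligibility criteria with any further baseline documentation". It "will be used to describe patient demographics and other baseline characteristics shown in Table 3".
- The FAS is the part of the BAS "with documentation from at least one time point post-baseline". Its scope is everything else: "All other statistical analyses will be performed on data from the" FAS.

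The primary analysis is described directly after this rule and covers "usage of peri- and post-procedural antithrombotic therapies, as well as other relevant concomitant medications at baseline and the two follow-up time points". The clinical events of interest and the ADRs follow, and no other set is named for them.

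Table 3 (Schedule section) marks concomitant medication, edoxaban intake, clinical events (bleeding, stroke, MI, PCI, death) and suspected ADRs for collection at baseline as well as at both follow-ups. The Bleeding events section adds that ISTH grading is used at baseline, in hospital. Follow-up bleeding is put into patient-friendly categories by telephone.

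**The concern.** Membership of the FAS depends on something that happens after the data in question were recorded. Peri-procedural therapy and in-hospital events are known at baseline, but a patient counts towards them only if a later form exists. Someone who withdraws, dies or cannot be traced after baseline, and for whom nothing later is documented, leaves both numerator and denominator.

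Three things are at stake:

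- The peri-procedural part of the primary objective would be described in a subset selected on later contact.
- The baseline bleeds, the only ones graded by ISTH, pass through the same filter.
- If patients lost early are also at higher risk, early rates are biased downwards. The Discussion already expects under-reporting of bleeding at follow-up, so the two errors would act in the same direction.

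This is a rule the article states, not a detail left to the analysis plan. An analysis plan that follows the article inherits it.

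**Working it through.** **Inputs.** From Sample size calculations: p = 17% (major or CRNM bleeding), n = 720, stated precision ±2.7 points and 16.1% relative. Assumed, because the documents give no figures: the share L of patients with no later documentation (2%, 5%, 10%), and the ratio r of their event risk to that of retained patients (1, 1.5, 2). The BAS is taken as all 720.

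**Step 1, the plan's own figure.** Wald half-width = 1.96 × √(0.17 × 0.83 / 720) = 2.74 points, and 2.74 / 17 = 16.1%. The stated figure is reproduced. It assumes that all 720 enrolled patients are analysed.

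**Step 2, precision after loss.** Replace 720 by 720 × (1 − L).

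**Step 3, selection.** If the true rate in the BAS is p, the rate among retained patients is p / [(1 − L) + L × r].

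| L | n in FAS | Half-width (points) | FAS rate, r = 1 | r = 1.5 | r = 2 |
|---|---|---|---|---|---|
| 2% | 706 | 2.77 | 17.0% | 16.8% | 16.7% |
| 5% | 684 | 2.82 | 17.0% | 16.6% | 16.2% |
| 10% | 648 | 2.89 | 17.0% | 16.2% | 15.5% |

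Example: 0.17 / (0.90 + 0.10 × 2) = 0.17 / 1.10 = 15.5%, a shift of 1.5 points.

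**Step 4, rates other than 17%.** The documents give no in-hospital rate, but the relative understatement, 1 − 1 / [(1 − L) + L × r], does not depend on the level of the rate. At r = 2 it is 1 − 1/1.02 = 2%, 1 − 1/1.05 = 5% and 1 − 1/1.10 = 9%.

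**Reading the table.** Precision hardly changes. The issue is who is in the denominator, and at equal risk there is no bias in the rates at all. The 17% is only a yardstick: it is an ISTH-graded rate from a randomised trial, whereas bleeding at follow-up is categorised differently here. A shift near the stated half-width needs stronger assumptions: at 10% loss and r = 3, 0.17 / 1.20 = 14.2%, or 2.8 points.

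**The case against.** The case on the other side has four parts.

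1. **The BAS clause.** It covers the other baseline characteristics in Table 3, and the baseline column of that table includes medication, edoxaban intake, events and ADRs. On a broad reading, the baseline data of early losses would still be described. This stands as an ambiguity. It does not settle the matter, because the primary analysis sentence names baseline therapy explicitly and falls under the FAS rule.
2. **Early losses can be recovered.** Relatives or the primary care doctor may be contacted, attempts continue to 1 year after a missed 30-day contact, and observations are to be completed up to the date of a consent withdrawal. This stands and makes L smaller. The article does not say whether a termination or withdrawal record counts as post-baseline documentation.
3. **Disposition will show the numbers.** Counts in each set with reasons for exclusion are planned, so a reader can see how many patients are missing. That shows the extent of the loss but does not restore their data.
4. **The shift is small** next to the sampling error. On the assumptions above, this stands.

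A reader might also infer more: that patients who never took edoxaban sit in the edoxaban safety denominator, since the disposition counts "patients who did or did not receive at least one dose of edoxaban post Index PCI" and no set is conditioned on a dose. The documents do not support that. FAS patients must meet the eligibility criterion "Having NVAF treated with edoxaban", and the count is made in the APS, which can include ineligible patients. At most, some FAS patients may have had no edoxaban dose after the index PCI, and their number may be zero. On-treatment summaries are commonly left to the analysis plan. Nor would restricting the main safety analysis to patients with a post-PCI dose be an improvement: observation starts 4 to 72 hours after PCI, so the restriction could remove someone who bleeds or dies before restarting, which is again selection on later information.

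**Conclusion.** The point holds in a limited form. As written, the FAS rule takes patients with baseline documentation only out of the peri-procedural part of the primary analysis and out of the event and ADR rates, although the data exist. The direction is downward if those patients have a higher early risk, and there is no bias in the rates if they do not.

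The size cannot be derived from the documents. Under an assumed 2–10% loss at up to twice the risk it is 0 to about 1.5 points on a 17% rate, or up to 9% in relative terms, and is probably small. That patients at higher risk are lost first is plausible but not shown.

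The wording does not establish that all baseline information on early losses is discarded, because the BAS clause may retain some of it, nor that every early death disappears, because proxy contacts are allowed. It gives no ground for a finding about never-dosed patients. The case for change is that the correction is specific and nearly free, not that the expected error is large.

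**What to change.** Amend the analysis-set wording, before database lock, to state that:

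- baseline and peri-procedural antithrombotic therapy, in-hospital clinical events and ADRs recorded at baseline are analysed in the BAS;
- Kaplan–Meier analyses of clinical events start from the BAS, with censoring at last contact, so that patients with baseline data only contribute their in-hospital time;
- the FAS is kept for summaries that need follow-up data;
- the clause on other baseline characteristics in Table 3 means a named list of items, and it is specified whether a termination or withdrawal record counts as post-baseline documentation.

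This removes selection at entry to the analysis. It does not recover events after last contact, and censoring there still assumes that loss is unrelated to risk. A supplementary summary by edoxaban exposure, in support of the objective "to investigate the effectiveness and safety of edoxaban in combination with antiplatelet therapy up to 1 year after a successful PCI", would be optional.

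Cost: a few sentences and no new data collection. The downside is that denominators will differ between tables and each must be labelled.
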